## Abstract

**Background:**

A clinical pattern of damage to the auditory, visual, and vestibular sensorimotor systems, known as multi-sensory impairment, affects roughly 2% of the US population each year. Within the population of US military service members exposed to mild traumatic brain injury (mTBI), 15–44% will develop multi-sensory impairment following a mild traumatic brain injury. In the US civilian population, multi-sensory impairment-related symptoms are also a common sequela of damage to the vestibular system and affect ~ 300–500/100,000 population. Vestibular rehabilitation is recognized as a critical component of the management of multi-sensory impairment. Unfortunately, the current clinical practice guidelines for the delivery of vestibular rehabilitation are not evidence-based and primarily rely on expert opinion. The focus of this trial is gaze stability training, which represents the unique component of vestibular rehabilitation. The aim of the Incremental Velocity Error as a New Treatment in Vestibular Rehabilitation (INVENT VPT) trial is to assess the efficacy of a non-invasive, incremental vestibular adaptation training device for normalizing the response of the vestibulo-ocular reflex.

**Methods:**

The INVENT VPT Trial is a multi-center randomized controlled crossover trial in which military service members with mTBI and civilian patients with vestibular hypofunction are randomized to begin traditional vestibular rehabilitation or incremental vestibular adaptation and then cross over to the alternate intervention after a prescribed washout period. Vestibulo-ocular reflex function and other functional outcomes are measured to identify the best means to improve the delivery of vestibular rehabilitation. We incorporate ecologically valid outcome measures that address the common symptoms experienced in those with vestibular pathology and multi-sensory impairment.

**Discussion:**

The INVENT VPT Trial will directly impact the health care delivery of vestibular rehabilitation in patients suffering from multi-sensory impairment in three critical ways: (1) compare optimized traditional methods of vestibular rehabilitation to a novel device that is hypothesized to improve vestibulo-ocular reflex performance, (2) isolate the ideal dosing of vestibular rehabilitation considering patient burden and compliance rates, and (3) examine whether recovery of the vestibulo-ocular reflex can be predicted in participants with vestibular symptoms.

**Trial registration:**

ClinicalTrials.gov NCT03846830. Registered on 20 February 2019.

## Administrative information

Note: the numbers in curly brackets in this protocol refer to SPIRIT checklist item numbers. The order of the items has been modified to group similar items (see https://www.spirit-statement.org/).

## Introduction

### Background and rationale {6a}

Exposure to brain injury via blast or blunt mechanisms disrupts multiple sensorimotor systems simultaneously. Veterans from both the Gulf War and Operation Iraqi Freedom/Operation Enduring Freedom (OIF/OEF) campaigns in addition to active-duty service members report physical, sensory, cognitive, and behavioral/emotional changes [1–4]. Typically, symptoms related to these damaged systems recover within weeks, and resolution is often seen within 3 months [4]. However, a significant portion of the population of wounded soldiers suffer long-term functional consequences including visual deficits, postural and locomotor instabilities, disorientation, dizziness, sensitivity to visual and body motion, and an impaired ability to read. Many of these symptoms are overlooked in patients with polytrauma [5]. Earlier descriptions of such symptoms reported a third of service members (SM) exposed to blast trauma had combined visual and hearing impairment, termed dual sensory impairment [6, 7]. More recent evidence suggests that within the population of soldiers exposed to traumatic brain injury, a clinical pattern of damage to the auditory, visual, and vestibular sensorimotor systems has emerged, which has collectively been given the name multi-sensory impairment (MSI) [8, 9].

Nearly 20% of veterans diagnosed with the mild form of traumatic brain injury (mTBI) have MSI, as examined from a database of > 13,700 veterans [8, 10]. More than 350,000 US Gulf War era and OIF/OEF veterans with mTBI are suffering from MSI [10–12]. Among a variety of predictors (i.e., older age, female gender, posttraumatic stress disorder), having a prior history of mTBI was the most robust at predicting MSI. Among active-duty SM, 15–25% deployed to Iraq or Afghanistan sustained an mTBI during their tour, though other studies have reported a larger percentage (44%) [2–5]. In the US civilian population, MSI-related symptoms are also a common sequela of damage to the vestibular system and mTBI affecting approximately 300–500/100,000 population [13, 14]. Irrespective of the environment (military or civilian) or cause (mTBI or peripheral vestibular injury), the inner ear is commonly damaged when symptoms of MSI are experienced that involve both hearing (conductive, sensorineural, or mixed) and vestibular loss [15, 16].

### Objectives {7}

The four aims of the INVENT VPT Trial are to:
Aim I: compare gaze and gait stability outcome measures between a novel (incremental velocity error (IVE)) and standard of care vestibular rehabilitation (VPT) interventionAim II: compare the unique effect of gaze stability training only (delivered via IVE or VPT) on posture and gait outcome measuresAim III: investigate the optimal frequency of gaze stability exercises taking into account the burden on the patient and current best evidenceAim IV: characterize inter-trial correlations of the gain of the vestibulo-ocular reflex (VOR), which may predict the likelihood of vestibular adaptation in both mTBI and civilians with unilateral vestibular hypofunction (UVH)

### Trial design {8}

INVENT VPT is a randomized controlled crossover trial in which participants are allocated in a 1:1 ratio to initially receive the current standard of care vestibular rehabilitation method based on recent clinical practice guidelines (VPT) or incremental vestibular adaptation training (IVE). The novel incremental velocity error (IVE) method of vestibular training uses a device developed from laboratory studies to increase/normalize the gain/response of the vestibulo-ocular reflex (VOR).

Aims I–III include a crossover design with a washout period—though the duration of the aims and washout periods vary. After the washout period, participants will then receive IVE (if randomized to initially receive VPT) or VPT (if randomized to initially receive IVE). The outcome measures recorded after the washout on the 1st return visit are incorporated into the respective training for both arms. For example, participants are given balance exercises depending on their functional ability, which may change if the arm provides such an effect thereby minimizing any carryover effect during washout. Each participant recruited for the INVENT VPT Trial will receive a home exercise program to complete and be seen weekly in the clinic for exercise progression. The home exercises consist of gaze stability training (IVE or VPT) and gait/balance exercises. Exercises (gaze stability and gait/balance exercises) within the VPT intervention are developed based on the clinical practice guidelines [17]. Participants receiving IVE will use the IVE device and perform the same gait/balance exercises as participants receiving VPT. Each aim will include newly recruited participants so participants from one aim will not be eligible to participate in subsequent aims. Aim IV is an exploratory aim using data from all three prior aims. There is no additional data collection for aim IV.

## Methods: participants, interventions, and outcomes

### Study setting {9}

INVENT VPT data collection will occur at two clinical centers in the USA. Active-duty SM will be recruited from patients attending the Fort Belvoir Community Hospital (FBCH) in Fort Belvoir, VA. Civilians will be recruited among patients at the Johns Hopkins University (JHU) School of Medicine Outpatient Center in Baltimore, MD.

### Eligibility criteria {10}

The following are the inclusion criteria:
Age 18–83 years oldService members with mTBI and civilian patients with vestibular hypofunction, both of which must report vestibular symptoms (i.e., dizziness, imbalance)Visual acuity with correction is ≥ 70 Early Treatment Diabetic Retinopathy Study (ETDRS) letter score (right and left eye)Visual acuity without correction is ≥ 35 ETDRS letter score (right and left eye)Participant has been diagnosed with a mild traumatic brain injury (FBCH site)Participant has been diagnosed with vestibular hypofunction (JHU site)Systolic blood pressure is ≤ 200 mmHg and/or diastolic is ≤ 110 mmHg at rest

The following are the exclusion criteria:
Any person with a self-reported history of significant ophthalmic, neuromuscular, cardiovascular (except hypertension), renal/electrolyte, and Meniere’s diseasePersons with uncontrolled severe hypertension (systolic blood pressure of > 200 mmHg and/or a diastolic blood pressure of > 110 mmHg at rest)Persons with a recent history of alcohol and/or drug abuse within the past 6 monthsPersons with benign paroxysmal positional vertigoCervical spine active range of motion < 45°

### Who will take informed consent? {26a}

Certified study coordinators at each clinical center will introduce the trial to potential participants and will provide a brochure and consent document that describes the study procedures. Initial discussions will occur between the study coordinator and the potential participant and study investigators will also be available to discuss INVENT VPT aims and procedures.

### Additional consent provisions for collection and use of participant data and biological specimens {26b}

Participants are notified at the time of consent for the trial that their data may be shared even after the study ends with research collaborators, the sponsor, or through government or other databases or repositories. Data will be shared without personal identifiers. No ancillary studies are planned for the INVENT VPT Trial.

### Interventions

#### Explanation for the choice of comparators {6b}

##### IVE

The IVE experimental comparator incorporates a portable device with micro-electronics that allows the training to be unassisted and performed at home. The device consists of a head unit and a base unit (Fig. 1). The head unit contains inertial sensors to measure the instantaneous 3-D orientation of the head in space at 250 Hz and an integrated circuit mirror to dynamically control the position of a laser target in space. The base unit consists of a touch screen interface that allows users to calibrate and set the device, in addition to recording compliance [18].

**Fig. 1 Fig1:**
[figure not shown]
A participant wearing the head unit of the IVE training device. The base unit illustrates the configuration screens

##### VPT

The VPT control group will participate in gaze stability training per the current standard of care, which involves a set of active head rotation exercises to be performed daily [17].

#### Intervention description {11a}

For aim I, we will randomize participants to the control (VPT) or experimental (IVE) group. For the following 6 weeks, participants in each group will be seen weekly for the progression of their gaze and gait stability exercises. Gaze stability will be for a total of 15 min per day for each group. After 6 weeks, participants will enter the washout stage for 6 weeks and not perform any explicit rehabilitation. Following the washout, participants will cross over into the other treatment group and complete another 6 weeks of IVE or VPT rehabilitation (Fig. 2).

**Fig. 2 Fig2:**
[figure not shown]
Algorithm of aim I comparing IVE with VPT, considering 6-week washout and crossover design. Both groups get gait/balance exercises from the beginning. CPG, clinical practice guidelines [17]

For aims II and III, we will also randomize participants initially to the IVE or VPT group with a washout period and crossover to the other intervention. As with aim I, each group from aim II and aim III will participate in rehabilitation at home and will visit the clinic once per week for the modification of the gaze stability exercises. However, participants in aims II and III will have a shortened participation and washout. The duration for participation in aims II and III is reduced from aim I based on our desire to determine ideal dosing for gaze stability training considering burden and compliance. Additionally, the expectation for most patients undergoing vestibular rehabilitation is that 6 weeks is a typical time to expect change (per currently clinical practice guidelines (CPG)) [17].

In aim II, neither IVE nor VPT groups will complete their balance and gait exercises until the washout period begins (Fig. 3). Each group will perform daily gaze stability exercises: VPT control group will follow the recommended CPG (15 min), and members in the IVE group will use the IVE device (15 min). Participants will perform the gaze stability exercises only for 3 weeks, before entering the washout stage for 3 weeks and not perform any explicit rehabilitation. Once they enter washout, they will begin gait/balance home exercises. Once the washout is complete, they will cross over into the other group for gaze stability training and continue with gait/balance exercise and progression (Fig. 3).

**Fig. 3 Fig3:**
[figure not shown]
Algorithm of aim II examining how training gaze stability alone impacts improvement considering 3-week washout and crossover design. Gait/balance exercises do not start until after the washout

For aim III, we seek to identify a minimum effective dose of gaze stability training. To do this, IVE and VPT participants will each complete their respective gaze stability training every other day. Both groups will complete the same gait/balance exercises from the start of the aim. Excluding the duration, the flow of aim III (Fig. 3) is similar to aim I.

For all aims, the intensity of the exercise program will be determined at the baseline visit based on the validated findings of the Dizziness Handicap Inventory, gait speed, and functional gait assessment (Table 1). Scores on each of these assessments will be summed for a composite impairment score. The composite score will inform the development of the exercise program to address the severity of impairment.

**Table 1 Tab1:** Schedule of enrollment and assessments in the INVENT VPT Trial

Study period				
Enrollment/baseline and randomization	Interventions	Follow-up assessments		
		vHIT	Participative measures	Impairment measures
**Eligibility screen** **Informed consent** One-time VOR characterization • Videonystagmography • Ocular and cervical vestibular evoked myogenic potential • Rotary chair • Video head impulse test • Audiogram • Clinical vestibular exam • Static visual acuity • Seated blood pressure **Randomization** • Treatment intensity ♦ Dizziness Handicap Inventory ♦ Gait speed ♦ Functional gait assessment	**Aim I** IVE-VPT VPT-IVE 6-week washout	Weeks 1–6 Weeks 13–18 6 months	Weeks 1, 4, 6 Weeks 13, 16, 18 6 months	Weeks 1, 4, 6 Weeks 13, 16, 18 6 months
	**Aim II** IVE-VPT VPT-IVE 3-week washout	Weeks 1–3 Weeks 7–9 6 months	Weeks 1, 3 Weeks 7, 9 6 months	Weeks 1, 3 Weeks 7, 9 6 months
	**Aim III** IVE-VPT VPT-IVE 3-week washout	Weeks 1–3 Weeks 7–9 6 months	Weeks 1, 3 Weeks 7, 9 6 months	Weeks 1, 3 Weeks 7, 9 6 months

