## Assignment of interventions: allocation

### Sequence generation {16a}

Random assignments to VPT-IVE or IVE-VPT will be allocated on a 1:1 ratio via a computer-generated randomization schedule stratified by the clinical center and utilizing random permuted blocks of random sizes. Block sizes are not disclosed.

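### Aim III is worded as finding an optimal frequency and a minimum effective dose, but its only randomized contrast is IVE versus VPT at a single frequency

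*Protocol article*

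**What the plan says.** The protocol article makes the dosing claim in three places. Objectives {7} gives Aim III as investigating the optimal frequency of gaze stability exercises in the light of patient burden and current best evidence. Intervention description {11a} goes further: "we seek to identify a minimum effective dose of gaze stability training". The abstract's Discussion says the trial will "isolate the ideal dosing of vestibular rehabilitation considering patient burden and compliance rates".

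The means offered, in {11a}, is that "IVE and VPT participants will each complete their respective gaze stability training every other day". Sequence generation {16a} sets out what is randomized: "Random assignments to VPT-IVE or IVE-VPT will be allocated on a 1:1 ratio via a computer-generated randomization schedule stratified by the clinical center". Trial design {8} separates the cohorts: "Each aim will include newly recruited participants so participants from one aim will not be eligible to participate in subsequent aims".

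Daily training occurs in the other aims. For Aim I, "Gaze stability will be for a total of 15 min per day for each group"; Aim II is also daily at 15 min. Section {11a} adds that "participants in aims II and III will have a shortened participation and washout", and explains the shorter duration by the wish to determine ideal dosing.

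**The concern.** To learn which frequency is best, or how little training still works, participants have to be compared at different frequencies. Aim III has one frequency, so its randomized comparison can show whether IVE and VPT differ at that frequency and nothing about the frequency itself. Daily training is seen only in other people, in other aims, who were not allocated to it by chance.

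At stake is how Aim III is read. Improvement from baseline under every-other-day training, or no detectable IVE-VPT difference, could be taken as evidence that the reduced frequency is enough. Neither result would show that.

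**Working it through.** **1. The stated sample size.** Sample size {14} uses a pre-post difference of 0.19, SD 0.18 and power 0.8; {20a} gives two-sided α = 0.05. With a paired t-test the effect size is 0.19/0.18 = 1.056. At n = 9 the noncentrality is 1.056 × √9 = 3.17 on 8 df, giving power 0.79. Allowing for attrition, 9/(1 − 0.25) = 12. The stated 9 and 12 are reproduced to within rounding, and they size a pre-post change, not a contrast of frequencies.

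**2. What is randomized.** Enrolment is 24 + 24 = 48 per aim, and 48 × 3 = 144 in all. The randomized factor is sequence (IVE-VPT or VPT-IVE), stratified by center. The number randomized to a frequency, or to an aim, is 0.

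**3. The regimens in period 1** ({11a} and Table 1).

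| | Aim I | Aim II | Aim III |
|---|---|---|---|
| Gaze training | daily, 15 min | daily, 15 min | every other day, session length not given |
| Period length | 6 weeks | 3 weeks | 3 weeks |
| Washout | 6 weeks | 3 weeks | 3 weeks |
| Gait/balance exercise in period 1 | from the start | not until washout | from the start |
| vHIT in period 1 | weeks 1–6 | weeks 1–3 | weeks 1–3 |
| Participative and impairment measures in period 1 | weeks 1, 4, 6 | weeks 1, 3 | weeks 1, 3 |

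**4. Which cross-aim comparisons are possible.**
- Aim III against the full Aim I period: frequency and duration (3 versus 6 weeks) both differ.
- Aim III against weeks 1 to 3 of Aim I, period 1: duration is the same, gait/balance exercise starts at once in both, and washout has not yet happened. For vHIT this is the closest match. Participative and impairment measures have no week-3 value in Aim I, so it does not work for them.
- Aim III against Aim II, period 1: duration matches, but gait/balance exercise differs.
- All three compare separately recruited cohorts without randomization.

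**5. Why session length matters.** Daily training at 15 min for 3 weeks is 3 × 7 × 15 = 315 min. Every-other-day training gives 10 or 11 sessions in 21 days. At 15 min each (an assumption) that is 150 to 165 min, about half. At 30 min each (also an assumption) it would be 300 to 330 min, about the same total. Step 4's closest match isolates frequency at fixed session length only in the first case.

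**6. Number of levels.** Daily and every other day are two points. Even a randomized comparison of them could not locate the lowest frequency that works.

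**7. Precision, as illustration only.** Per aim, 24 participants start on each intervention; with 25% attrition, 24 × 0.75 = 18. A two-sample t-test with 18 per frequency and SD 0.18 has noncentrality (δ/0.18) × √(18/2) on 34 df. The article gives no expected difference between frequencies, so δ is assumed:

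| Assumed δ | Noncentrality | Power |
|---|---|---|
| 0.19 | 3.17 | 0.87 |
| 0.095 | 1.58 | 0.34 |
| 0.05 | 0.83 | 0.13 |

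The SD comes from healthy adults, so these figures only suggest that a modest frequency difference could easily be missed.

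**The case against.** Several points against the concern have force.

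- The objective itself is modest: it says investigate, and it draws on patient burden and outside evidence. This stands for the frequency wording. It does not cover the statement about identifying a minimum effective dose, which is tied directly to the single-frequency design.
- Dose in this protocol is broader than frequency. Duration was shortened deliberately as part of the dosing question, and the aims together hold three regimens: daily for 6 weeks, daily for 3 weeks, and every other day for 3 weeks. This stands, so duration should not be treated only as a nuisance. The regimens are still compared across non-randomized cohorts.
- A reader might infer that no frequency analysis is planned, because Statistical methods {20a} names none. That does not follow. The article is condensed and the analysis plan is not shown, so a cross-aim analysis may be specified there. It could not, however, supply randomization or another frequency level.
- A reader might infer that frequency is inevitably confounded with a two-fold difference in duration. For vHIT it is not, because weekly measurement allows weeks 1 to 3 of Aim I to be used.
- Nothing in the article proposes to read a null IVE-VPT difference as proof that less training suffices. That risk concerns later interpretation and is not a stated intention.

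**Conclusion.** Aim III's wording promises more than its design can give. The only randomized contrast in Aim III is IVE versus VPT at one frequency; 0 of 144 planned participants are randomized between frequencies, and the two frequencies available across aims cannot locate a minimum. This rests on what the article fixes about training frequency, allocation and separate recruitment, and needs no numerical assumption. The power figures above do rest on assumed differences and do not carry the conclusion.

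The stronger reading, that the trial or its primary analysis is invalid, is not supported: the randomized IVE-VPT comparison within each aim is untouched. The wording should be fixed, but this is not a defect that undermines the trial.

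**What to change.** - Reconcile the wording with the design: state Aim III as IVE versus VPT when gaze training is done every other day. Do not present a minimum effective dose, an optimal frequency or ideal dosing as conclusions that the randomized design supports. This applies to Objectives {7}, Intervention description {11a} and the abstract's Discussion.
- If frequency is to be described, pre-specify one comparison, labelled exploratory and non-randomized: weeks 1 to 3 of Aim I period 1 against Aim III period 1, within IVE and within VPT, adjusted for site and baseline gain of the vestibulo-ocular reflex.
- Limit that comparison to vHIT outcomes, for lack of a week-3 value of the other measures in Aim I.
- State the Aim III session length, and say whether it equals the 15 min of Aim I.
- If Aim II period 1 is also used, say that it matches on duration but differs in gait/balance exercise.

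The cost is a change of wording, one exploratory analysis on data already scheduled, and a weaker stated claim. No visit, treatment or sample size changes.

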#### Participative measures

The DHI measures a participant’s perception of how the dizziness impacts their life. The index considers the emotional, physical, and functional aspects of their quality of life. Clinical significance is defined as a decrease in the DHI of either 18 points or 42% from the pre-treatment level [19]. VPT is known to reduce DHI score [20–22].

The ABC is a self-reported instrument that asks participants to rate their confidence performing 16 activities of daily living [23, 24]. Scores range from 0 indicating no confidence to 100 indicating complete confidence in the participant’s ability to perform the task without losing their balance. Scores < 67% indicate a risk for falling and accurately classify people who fall 84% of the time [25]. The ABC has excellent test-retest reliability (*r* = 0.92), and VPT is known to improve the ABC score [26].

The NSI collects data on the symptoms experienced after an mTBI. We will follow the Department of Defense’s suggestion that an individual experiencing a minimum of 20% score improvement from baseline is considered significant [27].

The PGIC is a commonly used method to quantify the amount of improvement the patient believes has occurred since beginning treatment (i.e., intervention). The PGIC asks one question that is rated on a 7-point Likert scale. PGIC values of 6 or more correlate best with actual change [28].

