#### Impairment measures

Impairment domain measures include the dynamic visual acuity test (DVA), the instrumented stand and walk test (ISAW), vertical and torsional alignment nulling (VAN and TAN), and the following clinical measures that we will instrument using inertial measurement units (9 degrees of freedom sensors)
Functional gait assessment (FGA)Gait speedTandem walkModified clinical test for sensory integration of balance (mCTSIB)

The DVA test will measure visual acuity during active impulse head rotations. Participants will wear a headband with a rate sensor attached that triggers a flashing letter once head velocity crosses a predetermined threshold. Participants will generate a single head rotation to the right and left (impulses, separately) with performance being assessed from the size of the smallest letter the participant can identify [19].

The ISAW uses wireless sensors to measure a 30-s stand, 7-m walk, followed by a 180° turn. ISAW can distinguish soldiers with mTBI from healthy controls by their longer duration to turn (*p* < 0.001), their increased number of steps to complete a turn (*p* < 0.001), and their decreased peak velocities during the turn (*p* = 0.003) [28].

During vertical alignment nulling and torsional alignment nulling (VAN, TAN), the participant views one red and one blue line on the tablet screen through color-matched red and blue filters. The tests measure the perception of ocular alignment and are reliable and valid in conditions of otolith dysfunction.

The FGA is an 8-item scale that was developed to determine fall risk in older adults. Participants are scored on a 4-level ordinal score while they perform various ambulation tasks. Scores < 20 indicate an increased risk of falling in older adults.

The Patrol Exertion Multitask Test (PEMT) involves significant cognitive demands of situational awareness, memory, and decision-making under the physical stress of moderate exertion. The PEMT is a 12-min test where participants view a virtual patrolling scenario while responding to intermittent and unpredictable reaction timing cues. During this, they report visual clarity and perceived exertion. The PEMT has excellent interrater reliability for the assessment of cognitive (ICC 0.97), visual (ICC 0.99), and exertional (ICC 0.98) domains and can distinguish active-duty service members (SM) with mTBI from healthy control service members based on scores of visual clarity and reaction time [29].

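### The composite impairment score, as written, adds DHI (higher is worse) to FGA and gait speed (higher is better), so a participant worse on all three can score as less impaired

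*Protocol article*

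**What the plan says.** For all aims, Intervention description {11a} (the paragraph just before Table 1) bases exercise intensity at the baseline visit on three assessments: DHI, gait speed and FGA. Table 1 lists the same three under treatment intensity. The rule for combining them is "Scores on each of these assessments will be summed for a composite impairment score", and its purpose is given next: "The composite score will inform the development of the exercise program to address the severity of impairment".

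The direction of two components is given elsewhere in the article:

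- DHI, under Participative measures: "Clinical significance is defined as a decrease in the DHI of either 18 points or 42% from the pre-treatment level". Higher is therefore worse.
- FGA, under Impairment measures: "Scores < 20 indicate an increased risk of falling in older adults". Higher is therefore better. On its scale: "The FGA is an 8-item scale that was developed to determine fall risk in older adults", and "Participants are scored on a 4-level ordinal score while they perform various ambulation tasks".

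Gait speed is listed under Impairment measures without a unit or a scoring direction. The article nowhere mentions reversing a component, rescaling, or converting to severity categories before summing.

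**The concern.** A sum works as an impairment score only if every component rises with impairment. Here DHI rises with impairment and FGA falls, so each FGA point lost lowers the composite by one point. Poor gait makes a participant look better, and a large enough gait deficit cancels or outweighs worse dizziness.

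Scale is a second problem. A walking speed in m/s contributes almost nothing next to a questionnaire total, whereas in cm/s it contributes heavily. With no unit stated, two sites following the sentence could produce different composites.

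What is at stake is the starting exercise program. A participant with poor gait could begin on a program meant for someone less impaired, and a reader could not reproduce how intensity was set.

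**Working it through.** The article gives no numerical value for the composite, so there is no figure of the plan's own to reproduce. The check applies the stated rule.

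**Inputs from the article.** Three components, summed; DHI higher is worse; FGA higher is better; FGA has 8 items with 4 levels each.

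**Assumptions.** FGA levels scored 0 to 3, so the maximum is 8 × 3 = 24; gait speed in m/s with faster better; DHI maximum 100; a ceiling of 1.5 m/s for rescaling.

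**Step 1: condition for misordering.** Let participant B be worse than A by a DHI rise ΔD, an FGA loss ΔF and a speed loss Δg. Then

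composite(B) − composite(A) = ΔD − ΔF − Δg.

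B scores as less impaired whenever ΔF + Δg > ΔD.

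**Step 2: a worked pair.**

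| | DHI | FGA | Speed (m/s) | Literal sum |
|---|---|---|---|---|
| A | 40 | 22 | 1.2 | 63.2 |
| B | 45 | 14 | 0.8 | 59.8 |

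B is worse on all three, yet the difference is 5 − 8 − 0.4 = −3.4. Gait speed is not needed for the inversion: DHI plus FGA alone gives 62 for A and 59 for B. Scoring FGA levels 1 to 4 would add 8 to both and leave the order unchanged. With speed in cm/s the gap widens: 40 + 22 + 120 = 182 for A against 45 + 14 + 80 = 139 for B.

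**Step 3: the same pair, direction-aligned on 0–1 scales**, using DHI/100 + (24 − FGA)/24 + (1.5 − speed)/1.5.

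- A: 0.400 + 0.083 + 0.200 = 0.683
- B: 0.450 + 0.417 + 0.467 = 1.333 (rounded total)

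The order is now correct.

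**Step 4: weight of gait speed.** With an assumed spread of 1.0 m/s, its share of the summed range is 1/(100 + 24 + 1) = 0.8% in m/s and 100/(100 + 24 + 100) = 44.6% in cm/s.

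**Step 5: how often, under assumed distributions.** DHI mean 45, SD 15 to 25; FGA mean 18, SD 3 to 5; speed mean 1.0, SD 0.22 m/s; loading on a common severity factor 0.4 to 0.8. This makes 27 settings of 400,000 simulated pairs, with values clipped to plausible ranges. Among pairs in which one participant is worse on all three, the share tied or misordered ran from about 4% (DHI SD 25, FGA SD 3, loading 0.8) to about 18% (DHI SD 15, FGA SD 5, loading 0.4). A repeat run gave 4.2% to 18.0%.

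**Step 6: what the literal sum measures.** A separate simulation used DHI SD 20, an FGA maximum of 24 or 30, speed SD 0.25 m/s, and correlations of DHI with the two gait measures from 0 to −0.7. The literal sum correlated 0.97 to 0.99 with DHI, and gait speed carried about 0.02% of its variance. In m/s the composite is close to DHI alone, with FGA acting in the wrong direction.

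**The case against.** The strongest reply is that the text does not compel raw addition. The article refers to validated findings from the three assessments and calls the result an impairment score. That is compatible with giving each test severity points and summing those, which would need no further reversal. The article is condensed, it mentions a manual of procedures that is not shown, and a scoring key is a natural thing to keep there. This is possible. But the article does more than leave the rule out: it states an operation on the scores of each assessment, and that operation gives a wrong order. If the manual converts to points, the sentence still misdescribes it.

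The second reply is that little follows from a misranking, and most of this stands:

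- The composite only informs the program, and no cut-points are given, so no individual can be shown to receive a different program.
- In aim I, "participants in each group will be seen weekly for the progression of their gaze and gait stability exercises", and aims II and III also have weekly clinic visits.
- Trial design {8} says that measures at the first visit after washout feed into training in both arms.
- Gaze-training time (15 min daily in aims I and II) and its frequency (every other day in aim III) do not depend on the composite. In aim II, gait and balance exercises do not begin until washout.
- The composite is neither an outcome nor a variable in the analysis model.

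The third reply concerns the numbers. The worked pair was chosen to invert, and the article gives no means, SDs, correlations or gait-speed unit. That is correct. The 4% to 18% is a share of pairs, not of participants wrongly treated, and it includes ties; on the same assumptions 82% to 96% of those pairs are ordered correctly. The FGA cut of 20 is stated for older adults, while eligibility runs from 18 to 83 years, so it should not be read as a fall-risk label for every participant. None of this affects the direction conflict, which comes from the article itself.

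**Conclusion.** The point holds as a low-severity error in the text. Followed literally, the stated rule can rank a participant who is worse on DHI, FGA and gait speed as less impaired. This rests only on the article's own directions for DHI and FGA. The 3.4-point inversion is an illustration, and the 4% to 18% frequency depends on assumed distributions. The dependence on units (0.8% against about 45% of the summed range) depends on the assumed 1.0 m/s spread and DHI and FGA maxima.

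The consequence is confined to how starting exercise intensity is set and whether it can be reproduced. The rule applies equally to both sequences, so it does not bias the VOR gain comparison, and it has no bearing on the sample size. Confidence is medium, because the unseen manual may already score the components properly.

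**What to change.** Reverse FGA and gait speed so that higher means more impaired on every component. Then either put all three on a common scale before summing, or convert each to severity points and sum the points. State the gait-speed unit and correct the sentence in Intervention description {11a} accordingly. If the manual of procedures already does this, the sentence should say so. Cut-points and exercise content remain the sponsor's clinical decision.

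The cost is one scoring definition and one wording correction, with no new assessment, visit or analysis.
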